### Fidelity evaluation

To ensure fidelity of delivery of the intervention, we will request intervention providers’ and participants’ consent to record intervention sessions (audio or video recording depending on the platform used and participants’ preference). When this is not possible, intervention providers will keep detailed notes. Intervention providers will also complete an intervention record form during/after each session, detailing the content of the therapeutic interaction. We anticipate 48 observations (up to 12 participants (4 per intervention provider) each receiving approximately 4 sessions) will be sufficient to identify intervention manual deviations and skills that require addressing in training for the definitive RCT trial.

A fidelity checklist will be completed based on the Conceptual Framework for Implementation Fidelity [43] for each case exploring adherence to the content, frequency, duration and coverage, and possible factors that moderate the adherence (e.g. intervention complexity, facilitation strategies, quality of delivery, responsiveness). A sample of data from the intervention record forms, from observations, and from case notes of interventions will be used to complete the checklists to identify where and how the intervention delivery deviated from that described in the intervention manual.

Findings will be used to refine the logic model, intervention documents, and training packages delivered to clinical team members and intervention providers for the clinical pathway, as necessary. We will develop and refine fidelity tools for the definitive trial and codebook for audio/video analysis of intervention delivery, based on work by Borrelli [44].

### Statistical analysis

In part 1, descriptive statistics and frequencies will be computed using STATA software to describe screening usage by calculating the proportions of participants who completed the screening in different settings and devices and the frequency and type of support and reminders provided. The proportions of participants with no cognitive problems, mild cognitive problems, or moderate and severe cognitive problems will be computed using pre-determined cut-offs [24, 25] and data from previous work [21], and assessment of scale cut-offs will be made.

A full statistical and health economics analysis plan for part 2 will be written and agreed by the programme management group and the Programme Steering Committee before data collection is completed. As this is a feasibility RCT, analysis will focus on assessing the feasibility criteria to determine whether to proceed to a definitive trial. Recruitment and retention figures will be calculated. This will include an assessment of the size of the eligible population and those that consent to participate. From this accumulated data, we will check the assumptions of the sample size calculation for the RCT. Statistical analysis plans for the RCT will also be finalised with knowledge of the format of the data collected. We will focus on the traffic light stop/review/go criteria [45, 46] to progress to the definitive trial, particularly on recruitment (go, average 12/month; review, average 6–11/month; stop, average ≤ 5/month) and retention (go, ≥ 80%; review, 50–79%; stop, ≤ 49%).

Descriptive statistics will also be computed to summarise questionnaire data overall and per group. Exploratory analysis will be conducted using the principle of intention to treat. A repeated measures ANOVA will be used to assess changes in the questionnaire measures over time. Adjusted mean differences will be reported to assess differences over time and between groups. Analysis will adjust for stratification variables. All estimates will be presented with 95% confidence intervals.

Data from individual participants and subgroups of participants will also be assessed to determine whether any participant, or subgroup of participants, has a larger or smaller magnitude of changes in the questionnaire measures compared with other participants. Any findings will be considered exploratory and will be considered for incorporation into the design of the definitive RCT.

We will evaluate the use of single work question instead of the full MS Work Difficulties questionnaire [39]. Correlation and reliability analyses will be computed between the total score of the MS Work Difficulties questionnaire and the single question. We will also evaluate the use of the Whooley Questions instead of the full PHQ-9. Correlation analysis will be computed between the total score of the PHQ-9 and the Whooley Questions.

Levels of missing data will be monitored and presented as part of the ongoing data collection, cleaning, and reporting processes. For validated outcome measures where rules are identified for handling missing data, these methods will be implemented. As this is a feasibility study, no further imputation will be applied to the data. Suitability of outcome measures will be determined by the level of completeness. Potential key outcome measures (e.g. Multiple Sclerosis Impact Scale-psychological subscale) for the definitive RCT will be deemed appropriate if minimum success criteria are achieved or if we can identify solutions to overcome any identified issue.

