In addition to feasibility outcomes, the following measures will also be used to capture information about the part 2 participants at baseline and 3 and 6 months after randomisation:Cognitive impairment assessed using Perceived Deficits Questionnaire [30]Quality of life assessed using Multiple Sclerosis Impact Scale [31] and EQ-5D-5L [32]Mood assessed using Patient Health Questionnaire-9 [33], Generalised Anxiety Disorder-7 scale [34], and Whooley Questions for depression screening [35]Functional ability assessed using Nottingham Extended Activities of Daily Living Scale [36]Self-efficacy assessed using Multiple Sclerosis Self-efficacy Scale [37]Service-use questionnaire, based on a measure used in other MS trials [38] and adapted for use in the NEuRoMS projectWork-related issues assessed using Multiple Sclerosis Work Difficulties Questionnaire Short Form [39]The extent to which work and medication adherence have been impacted by cognitive problems assessed using two single bespoke questionsCapability and wellbeing for health economics evaluation assessed using the ICEpop CAPability measure for Adults (ICECAP-A) [40].

We chose these measures because they (i) tap the domains of interest identified by our patient and public involvement (PPI) group (ii), were endorsed by our PPI partners, (iii) have good psychometric properties and are routinely applied in MS research, and (iv) are brief and easy to complete.

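### The planned repeated measures ANOVA, in its usual form, compares the groups less precisely than the collected data allow; a baseline-adjusted mixed model on all available follow-up scores would do better

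*Protocol article*

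**What the plan says.** The Outcomes section of the protocol article says the questionnaires will "capture information about the part 2 participants at baseline and 3 and 6 months after randomisation". The Statistical analysis section then fixes five things about them:

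- The model: "A repeated measures ANOVA will be used to assess changes in the questionnaire measures over time".
- The principle: "Exploratory analysis will be conducted using the principle of intention to treat".
- The estimates: "Adjusted mean differences will be reported to assess differences over time and between groups", with 95% confidence intervals.
- The covariates: "Analysis will adjust for stratification variables". The Randomisation and blinding section names site as the only stratification factor. The baseline score is not named as a covariate.
- Missing data: "For validated outcome measures where rules are identified for handling missing data, these methods will be implemented". Beyond that, "As this is a feasibility study, no further imputation will be applied to the data".

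The section does not say whether baseline is a level of the time factor or a covariate, nor what happens to a participant who misses a visit. It says that a full part 2 analysis plan will be agreed before data collection ends.

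**The concern.** The protocol names a particular model, so this is more than a detail left to the later analysis plan. Two features of that model, as it is normally fitted, work against the stated aims.

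First, an ANOVA of change over three visits, adjusted only for site, most naturally takes baseline as the first of three repeated outcomes. The treatment effect at 6 months is then the between-group difference in change from baseline. That contrast carries the full noise of the baseline score, whereas using baseline as a covariate removes only the part that predicts follow-up.

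Second, the classical one-row-per-participant form needs all three scores. Without imputation, someone with baseline and 3-month data but no 6-month score leaves the model, although an observed outcome exists.

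At stake is the precision of the adjusted differences and, under the complete-case form, how many randomised participants they represent. With 60 participants the intervals will be wide in any case, so avoidable loss matters.

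**Working it through.** **Inputs from the protocol article.** There are 60 participants (Sample size), allocated 1:1 (Randomisation and blinding), so 30 per arm. There are three visits (Outcomes). Retention is rated go at 80% or more and review at 50–79% (Statistical analysis).

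**Inputs not given, so assumed.** SD = 1, with equal correlation rho between any two visits, from 0.3 to 0.8. Retention is taken to mean having a 6-month score. Site adjustment is left out of both sides of each comparison. The 60 rests on judgement with no formula, so there is no figure of the plan's own to reproduce.

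**Step 1: complete data, n = 30 per arm, effect at 6 months.**

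- Change contrast (baseline as a level of time): variance = 2(1 − rho) × 2/n.
- Baseline as a covariate: variance = (1 − rho²) × 2/n.
- Ratio = 2(1 − rho)/(1 − rho²) = 2/(1 + rho).

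At rho = 0.5, the change contrast has variance 2 × 0.5 × 2/30 = 0.0667 and 95% half-width 1.96 × √0.0667 = 0.506. The adjusted estimate has variance 0.75 × 2/30 = 0.050 and half-width 0.438. The ratio is 1.33.

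| rho | half-width, change | half-width, adjusted | variance ratio |
|---|---|---|---|
| 0.3 | 0.599 | 0.483 | 1.54 |
| 0.5 | 0.506 | 0.438 | 1.33 |
| 0.7 | 0.392 | 0.361 | 1.18 |
| 0.8 | 0.320 | 0.304 | 1.11 |

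**Step 2: who a complete-case fit excludes.** At exactly 80% retention, 60 × 0.20 = 12. At 50%, 60 × 0.50 = 30. These are minimums, because anyone who misses only the 3-month visit is also lost.

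**Step 3: both effects at 80% retention.** Assume 48 of 60 have all three scores, 6 have baseline and 3 months, and 6 have baseline only. The comparator is a likelihood model on all available scores with one common baseline mean for both arms. The deletion column compares the complete-case ANOVA with the same model on available data. The baseline column compares that available-data model with the comparator.

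| rho | half-width, complete-case ANOVA | half-width, likelihood model | total ratio | from deletion | from baseline |
|---|---|---|---|---|---|
| 0.3 | 0.669 | 0.538 | 1.55 | 1.08 | 1.43 |
| 0.5 | 0.566 | 0.487 | 1.35 | 1.06 | 1.27 |
| 0.7 | 0.438 | 0.400 | 1.20 | 1.05 | 1.14 |
| 0.8 | 0.358 | 0.336 | 1.14 | 1.04 | 1.09 |

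**Step 4: other patterns.** If a further 5–10% miss only the 3-month visit (45 or 42 complete), the total ratio runs from 1.21 to 1.76. At 50% retention with 24 complete, it runs from 1.47 to 1.95. In that last case deletion is the larger part (1.39 to 1.53, against 1.06 to 1.27 from baseline).

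**Step 5: is deletion inevitable?** No. In 200 simulated trials (rho = 0.6, 12 missing the 6-month score and 6 missing the 3-month score), an ANOVA fitted in long format with subject effects kept all 60 participants. The complete-case fit kept about 43. The mean standard errors were 0.254 and 0.274. The long-format fit still estimates a change contrast, so the loss in Step 1 remains.

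**The case against.** The strongest reply is that the protocol states neither feature. It nowhere says that incomplete participants are excluded, and Step 5 shows a form of the ANOVA that keeps them. It nowhere says that baseline is an outcome, and the promise of adjusted differences leaves room for it as a covariate. A full analysis plan is to follow. All of this stands, and it is why the point concerns the model in its usual form. It does not remove the point: the named model and the single named adjustment lead most naturally to the less efficient analysis.

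Three stronger readings are tempting and are not supported:

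- **That the plan contradicts intention to treat.** The text invokes the principle for an exploratory analysis, and analysing people as randomised can meet it with some outcomes missing. Complete-case exclusion would fall short of including everyone, but that exclusion is not stated. Nor does the 50–79% band show that such loss is accepted: it is a trigger for review.
- **That the treatment effect will be diluted.** A group main effect averaged over baseline and two follow-ups would recover only two thirds of a constant effect. The protocol does not say that this main effect will be reported as the treatment effect, and differences over time and between groups fit visit-specific contrasts equally well. The change contrast is inefficient rather than biased when visits are missing at random with respect to the scores.
- **That the definitive trial's sample size will rest on these estimates.** The Sample size section speaks only of parameter estimates. Standard deviations can come from the separate descriptive summaries, which the ANOVA does not touch.

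The analysis is also exploratory, and progression turns particularly on recruitment and retention. That limits the weight of the point.

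**Conclusion.** The concern holds as a matter of precision and of fit with the intention-to-treat aim. If baseline is a level of time, the variance of the 6-month comparison is 11% to 54% larger than it need be, for rho from 0.8 to 0.3, with no data missing. If incomplete participants are also dropped, the excess is 14% to 55% at 80% retention with 48 complete, and more with additional missed visits or lower retention. At 80% retention with 48 complete, the handling of baseline accounts for most of it.

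These sizes rest on assumed equal correlations and assumed missing-visit patterns, since the protocol gives neither. The likelihood-model figures also treat the covariance as known, so the gain realised with 60 participants may be somewhat smaller.

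No progression decision on recruitment or retention is affected. The change is still worth making, because adjusted differences with 95% intervals will be reported. The section also says that exploratory findings will be considered for the definitive design, although that sentence stands in the paragraph on individual and subgroup changes.

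**What to change.** Replace the repeated measures ANOVA with a likelihood-based linear mixed model for the 3- and 6-month scores:

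- Fixed effects for baseline score, site, time, arm and arm-by-time.
- An unstructured covariance across visits and a small-sample degrees-of-freedom correction.
- Participants analysed as randomised, including everyone with at least one follow-up score. Alternatively, baseline can be kept as an outcome with a common mean in both arms, so that all randomised participants enter. Randomisation justifies this, because baseline questionnaires are completed beforehand.
- The adjusted difference and 95% confidence interval reported at each follow-up.

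The analysis plan should also state the number of participants contributing at each visit.

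The cost is wording and a standard command in Stata, which the protocol already names for part 1. No new data are needed, and the no-imputation rule can stay. The downsides are slightly more complex modelling and reliance on a missing-at-random assumption, which should be stated.

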### Adverse events

The occurrence of an adverse event (AE) or serious adverse event (SAE) because of study participation is unlikely since the study involves completing standardised tasks and questionnaires and receiving a manualised non-pharmacological intervention with trained professionals. Indeed, this has been the case in other MS trials of a similar intervention [38]. AEs and SAEs such as hospitalisation, distress, and death, in relation to participating in this study, will be recorded; however, these are likely to be rare events due to the nature of the study. ‘Notable events’ (i.e. any events that are considered out of ordinary) occurring during cognitive screening, or the intervention, will be recorded and monitored by the intervention providers or researchers. Participants will be informed of all research activities prior to participating in the study; thus, there will be no deception.

The results of the screening will be discussed with the patient by a healthcare professional, and, therefore, any concerns about the screening results will be addressed by the clinician. It is possible that talking about cognitive difficulties may sometimes create distress for people with MS. This distress will be dealt with during the intervention sessions or interviews on an individual basis. The intervention will be delivered in a clinical environment by a trained intervention provider who will receive monthly supervision. Therefore, the overall risk has been assessed as minimal.

If a participant is identified as having a high score on the Patient Health Questionnaire-9 and Generalised Anxiety Disorder-7 scale as part of the part 2 patient-reported outcomes (≥ 15 indicative of severe anxiety and depression [41]), we will recommend that they contact their GP to discuss this further. This will not affect their participation in the study, and GPs will already be aware of patients’ involvement in the part 2 study.

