If a participant discloses information during the intervention sessions or during interviews indicating that they are at risk of self-harm, or discloses information about intention to harm others, the intervention provider and interviewer will follow the safeguarding policies of their employing organisation or local NHS Trust standard procedures. If the participant has responded to question 9 of the Patient Health Questionnaire-9 (“How often have you been bothered with … thoughts that you would be better off dead, or of hurting yourself”) with answer 3 (“Nearly every day”), when checked by the research team, this will be interpreted as a significant suicide risk and documented as an AE. The researcher will report the suicide risk to the principal investigator (PI) immediately. The PI/person delegated by PI will then deal with the situation as per local NHS Trust standard procedures. AEs and SAEs will be reviewed and monitored by the independent programme steering committee.

The interviews will be conducted by trained researchers who will follow a distress protocol in the event of distress during interviews [42]. Researchers will ensure they give sufficient time to participants for debriefing after the intervention sessions/interviews. Participants will be informed that they can end the study at any point. If the participant no longer wishes to continue and consent is withdrawn, the researcher will debrief the participant and provide support, as needed.

Patient participants will be advised in the participant information sheet to contact their general practitioner (GP) (and/or their occupational health/counselling services for clinician and intervention provider participants) if they feel distressed. Contact information of appropriate sources of support will be provided for patient participants who feel they need further information/support with respect to cognitive problems in MS. Participants and GPs of patient participants will also receive the contact details of the research team for enquiries about the research.

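### The planned correlation with the PHQ-9 total does not show whether the Whooley Questions still classify participants or track change, and the work-item analyses do not show detection of change (minor)

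*Protocol article*

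**What the plan says.** Two shortened measures are examined in the Statistical analysis section of the protocol article.

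- **Depression.** The aim is "We will also evaluate the use of the Whooley Questions instead of the full PHQ-9". The only analysis named is "Correlation analysis will be computed between the total score of the PHQ-9 and the Whooley Questions".
- **Work.** The aim is "We will evaluate the use of single work question instead of the full MS Work Difficulties questionnaire". Here two kinds of analysis are named: "Correlation and reliability analyses will be computed between the total score of the MS Work Difficulties questionnaire and the single question".

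Elsewhere the protocol shows what these measures are for. The Outcomes section lists "Whooley Questions for depression screening" beside the PHQ-9 under mood, collects all measures at baseline, 3 and 6 months, and describes the work item as a bespoke single question. The Adverse events section applies a cut to the PHQ-9 and GAD-7, "≥ 15 indicative of severe anxiety and depression", which leads to a recommendation to see the GP. It also says of the highest response to PHQ-9 item 9 that "this will be interpreted as a significant suicide risk and documented as an AE". The Statistical analysis section examines the questionnaire measures for change over time and between groups by repeated measures ANOVA.

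**The concern.** Whether a short tool can replace a longer one depends on what the longer one is used for. In this protocol the PHQ-9 sorts participants at a cut, supplies a single-item risk alert, and serves as a repeated outcome. A correlation with the total score measures how closely two sets of scores rise and fall together across people. It does not say how many participants above the cut the short tool would flag, whether those with an item-9 alert would be among them, or whether the two tools move together within a person over time.

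The work item raises only the last of these questions. No case cut-off is stated for the work scale, but the full scale is among the measures analysed for change. Association or reliability between one question and a multi-item total does not establish responsiveness.

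At stake is the evidence on measures carried into the definitive trial. Determining the suitability of outcome measures is a stated Part 2 objective (Table 1).

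**Working it through.** The protocol gives no target correlation, sensitivity or margin for these comparisons, so there is no figure of its own to reproduce. The checks below are illustrations.

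**Inputs from the protocol:** 60 participants in Part 2 (Sample size); PHQ-9 cut of 15 or more (Adverse events); assessments at baseline, 3 and 6 months (Outcomes); 80% retention as the go level (Statistical analysis).

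**Assumptions, not in the protocol:** bivariate normal scores; prevalence p of PHQ-9 at or above the cut of 20%, with 10% and 30% as a range; proportion f flagged by the screen of 20%, 40% or 50%; error variances in step 3.

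**1. Sensitivity for a given correlation.** With c and k the normal quantiles at 1 − p and 1 − f, let J = P(X > c, Y > k) under correlation r. Sensitivity = J / p and specificity = 1 − (f − J) / (1 − p). For p = 0.20:

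| f | r = 0.7 | r = 0.8 | r = 0.9 |
|---|---|---|---|
| 20% | 56.5% | 64.5% | 75.0% |
| 40% | 82% | 89.5% | 97% |
| 50% | 90% | 95% | 99% |

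At r = 0.8 the ends of the column are 0.1290 / 0.20 = 64.5% and 0.1899 / 0.20 = 95%. The matching specificities are 1 − (0.20 − 0.1290) / 0.80 = 91% and 1 − (0.50 − 0.1899) / 0.80 = 61%. At r = 0.8 with other prevalences, sensitivity runs from 79% to 98% (p = 10%) and from 53% to 90% (p = 30%) over the same values of f.

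**2. The same point if the Whooley result is scored yes/no.** The observed correlation with the total is then r × φ(k) / √(f(1 − f)), where r is the underlying correlation.

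- r = 0.9, f = 20%: 0.9 × 0.2800 / 0.4000 = 0.63, with sensitivity 75%.
- r = 0.8, f = 40%: 0.8 × 0.3863 / 0.4899 = 0.63, with sensitivity 89.5%.

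Two screens with the same observed correlation can therefore differ by about 15 percentage points in sensitivity.

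**3. Change.** Take a true score with baseline SD 1, true change with SD s, and measurement-error SDs of 0.3 (long form) and 0.6 (short form).

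- Correlation at one time point: 1 / √((1 + 0.09)(1 + 0.36)) = 0.82.
- Correlation of change: s² / √((s² + 0.18)(s² + 0.72)).
- s = 0.3: 0.09 / √(0.27 × 0.81) = 0.19.
- s = 0.5: 0.25 / √(0.43 × 0.97) = 0.39.

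A correlation of 0.82 at one time point can go with a change correlation of 0.19 to 0.39. This applies to either pair.

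**4. Precision available.** Exact (Clopper–Pearson) 95% intervals for sensitivity:

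- 60 participants, 10%: 6 cases, 5 detected, 36% to 99.6%.
- 60 participants, 20%: 12 cases, 11 detected, 62% to 99.8%.
- 60 participants, 30%: 18 cases, 16 detected, 65% to 98.6%.
- 48 participants (0.80 × 60), 20%: about 10 cases, 9 detected, 56% to 99.7%.

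The correlation is itself imprecise. By Fisher's z, r = 0.7 has a 95% interval of 0.54 to 0.81 with 60 participants.

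**The case against.** The strongest case against is that this is a small exploratory aim in a feasibility study, described in a condensed article. The protocol says it will evaluate the short forms and attaches no decision rule. It ties suitability of outcome measures to completeness, and interviews also inform the choice. A full analysis plan is promised before data collection is completed, and cross-tabulations or change scores could appear there. Intervals of 95% are already promised for all estimates. The text does not say which time points are correlated. A cut marking severe scores is not evidently the ideal reference for a depression screen, and about a dozen cases would estimate sensitivity poorly.

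Much of this stands, and it limits the point to a minor addition. It does not remove it: the protocol names a method for a substitution question, and that method tests neither use of the PHQ-9. Completeness and interview data do not test them either.

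A reader might infer four stronger things, which the protocol does not support.

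- *That many cases would be missed.* The lower sensitivities arise only if the screen flags few participants. The figures show that correlation does not determine sensitivity, not that it is low.
- *That the item-9 check and the planned evaluation conflict in this study.* They do not. The full PHQ-9 is collected at every time point, so the check keeps its data source. The question arises only if a later trial drops the PHQ-9.
- *That the correlation decides which instruments go forward.* No passage says so.
- *That the work item is assessed by correlation alone, or that work cases would be lost.* Reliability analyses are also planned, and no work cut-off is stated.

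**Conclusion.** The point holds in a limited form. For the Whooley Questions, the one named analysis cannot show whether participants at or above the protocol's own cut are still identified or whether change is still tracked. At a correlation of 0.8, with bivariate normal scores and 20% at or above the cut, sensitivity of about 65% to 95% is possible over the flagging rates examined. For the work item, the planned analyses leave detection of change untested. The prevalence, flagging rates, distribution and error variances are assumptions and carry no information about this trial's data. Severity is minor: current participants, the progression criteria and the main feasibility results are unaffected.

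**What to change.** Keep the planned correlation and reliability analyses and add the following.

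1. A cross-classification of the Whooley result against a PHQ-9 score of 15 or more, the threshold the protocol already uses, with sensitivity, specificity and their 95% confidence intervals. Report beside it the number of item-9 alerts among Whooley-negative participants.
2. For both pairs (Whooley and PHQ-9; work item and full work scale), the correlation of change from baseline to 3 months and to 6 months.
3. A statement that with 60 participants these estimates are imprecise and cannot alone justify a substitution.
4. A statement that any proposal to drop the PHQ-9 in the definitive trial must be reconciled with the item-9 check described under Adverse events.

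The cost is a few lines in the analysis plan and two small tables from data already being collected. The downside is a few extra exploratory estimates with wide intervals.
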